## Abstract

Closed reduction is a common treatment method for developmental dysplasia of the hip (DDH) in children aged 6–18 months. Residual acetabular dysplasia (RAD) is the most common complication associated with closed reduction. Residual limbus inversion (RLI) is a common condition following DDH closed reduction. Previously, we confirmed that when limbus inversion exceeds 32.2% of the acetabular depth after closed reduction, RLI persists and leads to RAD; however, this was based on a small cohort with a short-term follow-up period. The long-term fate of RLI and the correlation between RLI and RAD have yet to be verified. Therefore, this multicenter clinical study protocol was designed in three parts to investigate the effect of RLI on acetabular development after closed reduction of DDH (a multicenter retrospective cohort study), effect of RLI clearance on acetabular development (a multicenter retrospective and prospective randomized controlled study), and influence of inverted limbus clearance on acetabular development during DDH reduction (a multicenter prospective cohort study). Statistical analysis was performed by assessing the basic measures of acetabular development including the acetabular index and central-edge angle using frontal pelvic radiographs; the magnitude of limbus inversion, cartilaginous acetabular index, and T1ρ mapping values were measured using magnetic resonance imaging. The multicenter retrospective cohort studies required 5 years of follow-up period at minimum, and the prospective randomized controlled studies required reviews of frontal pelvic radiographs every 6 months as well as data pooling every 2 years to compare the short- and mid-term outcomes of hip joint morphological development between the two groups of pediatric patients. This research program is expected to verify that RLI following closed reduction of DDH can affect acetabular development and that limbus excision during DDH reduction can improve postoperative RAD. Therefore, the indication and timing of surgical intervention for RLI after closed reduction of DDH provide a basis for revising the acceptable criteria for utilizing closed reduction of DDH to reduce the incidence of osteoarthritis caused by RAD following DDH treatment.

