##### Inclusion criteria

2.2.1.1.

1.Pediatric patients undergoing closed reduction at 6–18 months of age;2.No other treatment prior to DDH reduction, with or without the administration of pre-reduction traction or percutaneous adductor tenotomy;3.After DDH reduction, a Spica cast was applied to immobilize the hips in ≤65° of abduction for 3 months, followed by use of abduction braces for 3 months;4.Patients must have a successful closed reduction, defined as a stable reduction enabling femoral head-acetabulum concentricity as suggested by frontal pelvic radiographs taken at 9–12 months after DDH reduction;5.Follow-up for more than 5 years.

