##### Statistical analysis

2.2.1.4.

Statistical analysis was performed using SPSS 27.0 software (IBM, SPSS Inc.).
1.To ensure consistency and reliability between multicenter research samples, it is first necessary to conduct a consistency analysis on the structural data, such as age and sex, of the included cases from each center and the International Hip Dysplasia Institute (IHDI) classification using the Cohen's kappa statistic. Simultaneously, the baseline characteristics (such as structural composition and pathological severity) of the included cohorts within each center must be consistent; imbalances in baseline characteristics were corrected by increasing the sample size.2.The included patients were divided into the non-limbus inversion group (A) and the limbus inversion group based on the presence of limbus inversion at closed reduction. The limbus inversion group was then further divided into the RLI group (B) and the resolved inverted limbus group (C) according to the state at final follow-up. A combination consisting of any two of the groups was organized into cohorts. Fisher's precision probability test was used to compare the difference between the sexes and affected sides, using analysis of variance to compare the different ages between the two groups. Differences in acetabular index was compared using Student's *t*-test. Chi-square test was used to compare IHDI classification, VAS and HHS, and Severin classification at the final follow-up, and analysis of variance was used to compare the MRI T1ρ mapping values and the difference in the initial magnitude of limbus inversion between groups B and C, as well as the difference between the initial magnitude of limbus inversion and that at the final follow-up in group B.3.ROC curve analysis was used to predict the cut-off value of the initial magnitude of limbus inversion in the case of persistent RLI as well as calculate its specificity, sensitivity, and statistical significance.4.Sample size calculation.In this study, ossification of the acetabular cartilage was the main observation; thus, improvement of the acetabular index was the most suitable observation indicator. The sample size calculation was based on the previously published acetabular index at the final follow-up in the group with RLI and the group without RLI after closed reduction (21.41°±3.61° and 18.88 ° ± 4.32° in the two groups, respectively) (15). The significance level *α*, the statistical power of the test, the ratio of the sample sizes in the two groups, and the percentage of patients lost to follow-up were set at 0.05, 0.9, 1:1, and 20%, respectively. The minimum sample size for each group was calculated to be 67 cases (134 cases in total). Therefore, at least 67 cases needed to be enrolled in the observation group and the control group, respectively.

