##### Selection of participants for the retrospective study

2.2.2.1.

To maximize the use of the peak ossification potential of acetabular cartilages in patients before the age of 5 years, pediatric patients who underwent successful closed reduction between 6 and 18 months that had experienced RLI and were ≤5 years old at follow-up were selected as study participants, given that it is more instrumental to observe the reversibility of delayed acetabular cartilage ossification. The frontal pelvic radiographs and MRI images of the hip joint were taken during follow-up to evaluate limbus inversion. The trail is illustrated in a flowchart as shown in Figure 5.

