At present, the changes and outcomes of the inverted limbus after closed reduction of DDH remain controversial. Severin et al. (23) believed that after achieving stable closed reduction, the inverted limbus would be gradually absorbed and disappear; however, others believed that the inverted limbus was a key factor leading to AVN. Previous studies have been based on indirect observation of x-ray images, and there is a lack of direct evidence regarding the morphological evolution of the inverted limbus. This study used serial MRIs to observe the outcomes of limbus inversion after closed reduction of DDH, which lessened the impact of radiation on pediatric patients and enhanced the safety and reliability of the study. Our previous findings indicated that the magnitude of limbus inversion after closed reduction is closely related to its medium-term morphological outcome (16). However, the previous study had certain limitations since it was based on a small sample and did not follow-up until skeletal maturity. Previous studies have confirmed that a primary limbus inversion leads to primary acetabular dysplasia and early-onset OA (24, 25), but the long-term result of RLI has not been reported in DDH patients who previously underwent closed reduction.

Reaching skeletal maturity of the hip is a long-term process; therefore, the prospective design of this protocol better reflects the relationship between RLI and multiple prognostic outcomes while balancing many known or unknown biases. This research plan is to be led by the corresponding author's institution and carried out by multiple clinical research centers in cooperation with pediatric orthopedic centers in China. Compared to previous case-control studies, this study was designed as a multicenter clinical study with a higher level of evidence. Consistency of the characteristics included in a multicenter sample study is a key issue in clinical research. In the process of sample collection, cohort characteristics within each center are required to achieve homogeneity, which can be solved by increasing the sample size to ensure reliability of the final pooled samples. The follow-up rates in clinical studies are another key issue affecting reliability of the study results. Specialized staff in each center were assigned the task of following included cases, establishing case study databases, and recording various contact methods to guarantee a follow-up rate of over 80%.

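### Part 1 sets persistent versus resolved limbus status at an open-ended final follow-up and compares the acetabular index without allowing for follow-up time, which can bias B versus C and the ROC cut-off by an amount the document does not fix

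*Protocol article*

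**What the plan says.** Section 2.2.1.4 (item 2) forms group A from children without limbus inversion at closed reduction. The remainder are "further divided into the RLI group (B) and the resolved inverted limbus group (C) according to the state at final follow-up". Severin class is compared at the same final visit. The acetabular index is compared by Student's t-test. That sentence gives no time point, but item 4 does for the planning figures: "The sample size calculation was based on the previously published acetabular index at the final follow-up". Ages are compared between groups, without saying which age. Follow-up duration is not mentioned as something to compare, match or adjust for.

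The final visit is bounded on one side only. Section 2.2.1.1 requires "Follow-up for more than 5 years", and the Abstract agrees: "The multicenter retrospective cohort studies required 5 years of follow-up period at minimum". The same criteria list gives the age at reduction: "Pediatric patients undergoing closed reduction at 6–18 months of age".

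Item 3 derives an ROC cut-off of initial inversion for persistent RLI. Criterion 8 in 2.2.2.1.1 and the grouping rule in 2.2.3.2 both allow that cut-off to be used in place of 32%.

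The title of 2.2.1 speaks of long-term effects, and its text of mid- and long-term impact. The Discussion says of the earlier study that "it was based on a small sample and did not follow-up until skeletal maturity".

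**The concern.** Group label and outcome appear to be read at one visit whose timing differs from child to child. If an inverted limbus can still resolve after 5 years, a child followed longer is more likely to be labelled C. If the index also still falls after 5 years, that child has had longer to improve. Group C would then look better than B partly because it was watched longer, and a bare t-test cannot separate the two.

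The ROC analysis has the same weakness, since persistent would mean persistent for however long that child was followed. This matters beyond part 1, because the cut-off can feed into eligibility for part 2 and cohort assignment in part 3.

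A 5-year minimum also does not by itself secure a long-term result by the article's own yardstick of skeletal maturity.

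**Working it through.** **1. The plan's own figure.** Section 2.2.1.4 gives "21.41°±3.61° and 18.88 ° ± 4.32° in the two groups, respectively", α 0.05, power 0.9, ratio 1:1 and 20% loss.

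- Difference: 21.41 − 18.88 = 2.53°.
- Pooled SD: √((3.61² + 4.32²)/2) = 3.98°.
- n per group = 2 × (3.98 × (1.960 + 1.282)/2.53)² = 52.03, so 53.
- Allowing for loss: 53/0.8 = 66.25, so 67.

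The stated 67 per group (134 in total) is reproduced with a two-sided test.

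**2. Earliest final visit.** Reduction at 6–18 months plus 5 years gives an age of about 5.5–6.5 years. There is no latest age.

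**3. Effect of a spurious difference.** Take a true RLI effect of zero, 53 evaluable per group and SD 3.98°. The document does not give sizes for B and C, so 53 is borrowed from the plan's calculation. SE = 3.98 × √(2/53) = 0.773°. The chance of p < 0.05 is 1 − Φ(1.96 − bias/SE) + Φ(−1.96 − bias/SE).

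| Spurious difference | Share of 2.53° | Chance of significance |
|---|---|---|
| 0.25° | 10% | 6% |
| 0.5° | 20% | 10% |
| 1.0° | 40% | 25% |

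**4. What could produce such a difference.** Bias = (yearly fall in index) × (gap in mean follow-up). The document gives neither, so both are assumptions. At 0.5° per year, a gap of 1 year gives 0.5° and a gap of 2 years gives 1.0°.

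**5. Gap created by the labelling rule alone.** Assume resolution at a constant 0.05–0.2 per year and follow-up spread evenly from 5 years to a maximum. The gap is the mean follow-up of the resolved minus that of the unresolved.

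Example with rate 0.1 and maximum 12 years:
- Unresolved share: (e^−0.5 − e^−1.2)/(0.1 × 7) = 0.436.
- Mean follow-up of the unresolved: [(150 × e^−0.5 − 220 × e^−1.2)/7]/0.436 = 8.095 years.
- Mean follow-up of the resolved: (8.5 − 0.436 × 8.095)/0.564 = 8.813 years.
- Gap: 0.72 years.

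| Longest follow-up | Gap, C minus B | False positives at 0.25°/yr | at 0.5°/yr | at 1.0°/yr |
|---|---|---|---|---|
| 8 years | 0.13–0.20 yr | 5.0–5.1% | 5.1–5.2% | 5.3–5.8% |
| 12 years | 0.59–0.99 yr | 5.4–6.2% | 7–10% | 12–25% |
| 16 years | 1.25–2.19 yr | 7–11% | 13–30% | 37–81% |

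The answer therefore runs from nothing to substantial. It depends on the spread of follow-up and the late slope, neither of which is in the document.

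**The case against.** The article itself gives reasons to expect little late change. The Introduction reports that serial MRI showed the inverted limbus being compressed into a thin layer rather than disappearing. Section 2.2.2.1 refers to the "peak ossification potential of acetabular cartilages in patients before the age of 5 years", and every part 1 child is past that age at the final visit. No statement in the article shows limbus status still changing after 5 years. These points stand as reasons why the bias may be small. They do not remove it, because the plan provides for a resolved group and nothing keeps follow-up narrow.

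Adjustment for follow-up time could sit in an analysis plan that is not shown. That is fair for covariates. The B/C definition and the t-test, however, are stated here.

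Three stronger readings are tempting and are not supported:

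- **That the design is shown to create most of the planned effect.** Assuming a fall of 1.0° per year and a 3-year gap gives 3.0°, or 119% of 2.53°. Both inputs are unsupported. In the table above, the labelling rule alone gives a gap over 1 year only when follow-up reaches 16 years.
- **That every RLI contrast is biased towards harm.** Group A is fixed at reduction, so its membership does not depend on follow-up. A versus B is affected only if follow-up differs between those groups, for example by centre or calendar period. Excluding hips re-operated for RAD (2.2.1.2) could also pull the other way.
- **That the long-term claim is simply false.** Section 2.2.1 says mid- and long-term, and parts 2 and 3 provide for assessment at skeletal maturity.

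**Conclusion.** The point holds in a limited form. B/C status, Severin class and, by inference from the sample-size sentence, the acetabular index share a final visit that may fall at any time beyond 5 years, and the stated index test ignores that timing. If status or index still changes after 5 years, unequal follow-up can bias B versus C and the ROC cut-off that may pass to parts 2 and 3.

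The direction and size are not established. As a guide, a spurious 0.5° or 1.0° would be called significant about 10% or 25% of the time at 53 per group. The effect is near zero if follow-up is narrow or both quantities are stable. The sample size calculation is sound on its own inputs. This is a worthwhile and inexpensive improvement to the analysis, not evidence that part 1 will give a false result.

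**What to change.** In 2.2.1.4:

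1. Replace the t-test of the acetabular index with a linear model containing group, age at measurement and years since reduction, and state the visit at which the index is read.
2. Report follow-up time for groups A, B and C.
3. Add years since reduction to the ROC analysis of persistent RLI, for instance as a covariate in the regression behind the curve.
4. As a sensitivity analysis where imaging exists, repeat the B/C classification, the index comparison and the ROC at a common time since reduction within a stated window. This is needed because covariate adjustment does not by itself repair labels assigned at unequal times.
5. Describe results for children who are not yet skeletally mature as mid-term.

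The cost is one or two model degrees of freedom and a smaller sample in the sensitivity analysis. Making the common time point the primary analysis would be a real trade-off: 2.2.1.3 gives no imaging schedule for part 1, and the aim includes later outcomes. The planned 67 per group need not change on this account.

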## Introduction

1.

Closed reduction is a common method for treating developmental dysplasia of the hip (DDH) in children aged 6–8 months; however, re-dislocation after reduction, avascular necrosis, residual acetabular dysplasia (RAD), and other complications cannot be completely avoided (1). Among these, RAD is the most common complication of DDH closed reduction treatment. A prospective multicenter study conducted by Sankar et al. (2) found that even with stable closed reduction, approximately 11% of children still had residual dysplasia, and long-term follow-up results of a study by Terjesen (3) noted a higher statistic of up to 38%. RAD is the main cause of osteoarthritis (OA) in young adults (4, 5) which often requires total hip replacement (THR). Approximately 9.1% of THR is caused by RAD, and among young adults, this proportion is as high as 21%–29% (6, 7). Therefore, prevention of RAD after DDH treatment and timely correction of RAD are key to long-term prevention of OA.

The causes of RAD in children after closed reduction for DDH are complex. Age, dislocation height, and acetabular index at reduction are commonly used clinical indicators to predict RAD (3, 8, 9), but these factors can only partially explain the causes of RAD from clinical phenomena. Several factors affect the development of the acetabulum after closed reduction. In addition to the genetic quality of DDH, the quality and development potential of the acetabular cartilage, the soft tissue in the acetabulum, and the evolution of the concentric relationship between the acetabulum and femoral head are related to the shaping ability of the hip joint. A relevant understanding of the internal causes of RAD and timely intervention are of clinical significance for the prevention of OA caused by RAD. Previous clinical studies based on indirect radiological observations cannot directly reflect real world practice, in which the non-bone structure and concentric evolution of the hip joint must be considered. Radiological observations can be used to monitor acetabular development; however, they cannot accurately predict RAD (10, 11). Therefore, a method for follow-up observation of hip joint development is warranted to enable better clinical understanding of RAD.

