#### Long-term effects of RLI on acetabular development after closed reduction of DDH: a multicenter retrospective cohort study

2.2.1.

We retrospectively analyzed the outcomes of RLI as well as the mid- and long-term impact of RLI on acetabular development in DDH patients receiving closed reduction at different centers. The trail is illustrated in a flowchart as shown in Figure 2.

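### Part 1 compares acetabular index between non-assigned groups by an unadjusted t-test and treats a larger sample as the cure for baseline imbalance

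*Protocol article*

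**What the plan says.** Section 2.2.1 of the protocol article is titled "Long-term effects of RLI on acetabular development after closed reduction of DDH: a multicenter retrospective cohort study". Its stated subject is the "mid- and long-term impact of RLI on acetabular development in DDH patients receiving closed reduction at different centers".

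Section 2.2.1.4, item 2, forms three groups. Group A had no limbus inversion at closed reduction. The remaining cases are "further divided into the RLI group (B) and the resolved inverted limbus group (C) according to the state at final follow-up". Then: "A combination consisting of any two of the groups was organized into cohorts".

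For the outcome, the section states: "Differences in acetabular index was compared using Student's" *t*-test. Age is handled by "using analysis of variance to compare the different ages between the two groups". Sex and side are compared by Fisher's test and IHDI class by a chi-square test. No regression, analysis of covariance, matching, stratification or propensity method is named for part 1.

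Item 1 of the same section says that where baseline characteristics are out of balance, this is put right by a larger sample. The Discussion repeats the idea.

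The Introduction states: "Age, dislocation height, and acetabular index at reduction are commonly used clinical indicators to predict RAD".

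**The concern.** Membership of group A, B or C follows from the condition of the hip and its course, so the groups may differ in the factors that the article itself names as predictors of residual acetabular dysplasia (RAD). A hip that was worse at the start could have both a more inverted limbus and a worse later index. An unadjusted *t*-test credits the whole difference to RLI.

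Testing age and IHDI class for group differences describes such an imbalance but does not remove it from the outcome comparison. The stated remedy does not remove it either. More cases reduce chance imbalance, but a systematic difference between the groups stays the same size while the standard error shrinks. At stake is whether the part 1 estimate can be read as an effect of RLI at all.

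**Working it through.** **The plan's own figure.** Inputs from section 2.2.1.4, item 4: final acetabular index 21.41 (SD 3.61) with RLI and 18.88 (SD 4.32) without; alpha 0.05 (taken as two-sided), power 0.9, ratio 1:1, loss 20%.

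- Difference: 21.41 − 18.88 = 2.53 degrees.
- Common SD: √((3.61² + 4.32²)/2) = 3.98.
- n per group = 2 × (3.98 × (1.960 + 1.282)/2.53)² = 52.03, rounded up to 53.
- With loss: 53/0.8 = 66.25, rounded up to 67.

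The stated 67 per group reproduces. It is the size for an unadjusted comparison of two means, and about 53 of the 67 are expected to be analysable.

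**What bias is plausible.** The documents give no figure for group imbalance or for the link between severity and index, so these inputs are assumptions. Take an imbalance of 0.3 to 0.5 SD in a severity score that correlates 0.3 to 0.5 with final index.

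- Low: 0.3 × 0.3 × 3.98 = 0.36 degrees, or 14% of 2.53.
- High: 0.5 × 0.5 × 3.98 = 1.0 degree, or 39% of 2.53.

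**What that does to the test.** With no true RLI effect and bias b, the standard error is 3.98 × √(2/n). By the normal approximation, the chance of two-sided significance is 1 − Φ(1.96 − b/SE) + Φ(−1.96 − b/SE).

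| Analysed per group | SE | b = 0 | b = 0.5 | b = 1.0 |
|---|---|---|---|---|
| 53 | 0.773 | 5% | 10% | 25% |
| 134 | 0.486 | 5% | 18% | 54% |
| 500 | 0.252 | 5% | 51% | 98% |

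(The 134 here is per group, twice the planned 67; it is not the plan's total of 134.) The bias is constant down each column, and the false-positive rate rises with n.

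**What adjustment does to the sample size.** Let R² be the outcome variance explained by the covariates and Rx² the variance in group membership that they explain. Then n = 52.03 × (1 − R²)/(1 − Rx²), divided by 0.8 for loss. Both are assumed: R² 0.1 to 0.3, Rx² 0 to 0.2.

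- Most favourable: 52.03 × 0.7 = 36.4, so 37, then 47 per group.
- Least favourable: 52.03 × 0.9/0.8 = 58.5, so 59, then 74 per group.

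The planned 67 lies inside this range.

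**The case against.** The article is condensed. Section 4.2 mentions a data analysis plan that is not shown, and covariates are often left to such a plan. That would be a full answer if the article were merely silent. It is not: it names one test for this outcome and states how imbalance is dealt with, and the stated remedy cannot work against confounding. It may be said that the remedy concerns consistency within centres and not groups A to C. Then nothing at all is stated for imbalance between the groups.

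The entry criteria do limit confounding: reduction at 6–18 months, no earlier treatment, uniform cast and brace periods, successful reduction, no syndromic cases. This stands as partial control. Age can still differ threefold, and dislocation height and index at reduction remain free.

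The plan also calls improvement in the index the most suitable indicator. A change score would partly account for the starting value. But the section does not say that the *t*-test uses change, and the sample size rests on final values. Age and dislocation height would stay unadjusted either way.

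Three stronger readings are tempting, and the documents do not support them:

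- *That the Discussion's statement about bias is contradicted by part 1.* The sentence saying that the design "better reflects the relationship between RLI and multiple prognostic outcomes while balancing many known or unknown biases" is about the prospective design, so it makes no claim for the retrospective part.
- *That part 1 is the only test of the link between RLI and dysplasia.* Part 2 randomises children with RLI to clearance or no clearance and compares acetabular index. It does not compare RLI with no RLI, but it is randomised evidence on the same question.
- *That this *t*-test drives parts 2 and 3.* The cut-off passed to them (2.2.2.1.1, criterion 8; 2.2.3.2) comes from the ROC analysis of initial inversion against persistent RLI, and both parts can use the earlier 32% value.

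**Conclusion.** The point holds and should be fixed. As written, part 1 can credit baseline severity to RLI, and its stated remedy would make a spurious finding more likely, not less. Under assumed biases of 0.5 and 1.0 degree and no true effect, false significance occurs in about 10% and 25% of studies at 53 analysable per group, and in 18% and 54% at 134 per group.

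These rates rest on assumed biases; the documents neither show that the groups differ at baseline nor by how much. A reader might infer that a difference of the planned size would be wholly an artefact. That does not follow: even the largest bias assumed here leaves 61% of the 2.53 degrees. The sample-size figure is arithmetically sound; the fault is in the analysis method.

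**What to change.** In section 2.2.1.4:

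1. Make the main part 1 analysis a linear regression of acetabular index on group, adjusted for age at reduction, IHDI grade and centre.
2. For B versus C, add the initial magnitude of limbus inversion, which section 2.2.1.3 already measures on arthrography.
3. Show results with and without index at reduction. It predicts the outcome but may itself partly reflect inversion, so neither model alone settles the matter.
4. Keep the *t*-tests as descriptive.
5. Delete the statement that a larger sample corrects baseline imbalance, here and in the Discussion.
6. Report an adjusted association, not an effect. B and C are defined by state at final follow-up, and baseline covariates cannot repair that.

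The cost is small. Age, IHDI class and initial inversion are already collected, and index at reduction is needed for any measure of improvement. The price is a few degrees of freedom and the loss of children with a missing covariate. Under the assumed ranges above, 47 to 74 per group would be needed against the planned 67.

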##### Cohort grouping and interventions

2.2.3.2.

For cases meeting the assessment criteria specified in 2.3.1, the labral morphology was further evaluated using intraoperative arthrograms if there was no limbus inversion or if magnitude of the limbus inversion was <32% of the horizontal depth of the acetabular roof (or the cut-off value obtained in 2.2.1). A closed reduction using Spica cast immobilization was then performed to construct the control cohort. If intraoperative evaluation suggested that the magnitude of limbus inversion exceeded the cut-off, open reduction with post-reduction Spica cast immobilization was performed, in which the acetabular soft tissues were removed *via* the bikini incision approach, and the inverted limbus was excised. Patients undergoing open reduction procedures constituted the experimental cohort. Patients in the two cohorts underwent post-reduction cast immobilization for 3 months followed by immobilization with braces for 3 months.

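### Minor, free improvement: section 2.2.1.4 names Student's t-test for the acetabular index although the planning SDs differ and part 1 does not fix its group sizes; Welch's test would hold 5% whatever the ratio

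*Protocol article*

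**What the plan says.** Section 2.2.1.4, item 2, fixes the test for part 1: "Differences in acetabular index was compared using Student's" *t*-test. Sections 2.2.2.6 and 2.2.3.4 repeat the choice for parts 2 and 3. None of the three mentions a check of variances or an unequal-variance version. The software is named ("Statistical analysis was performed using SPSS 27.0 software").

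Item 4 of 2.2.1.4 calls the acetabular index the most suitable indicator and bases the sample size on published final follow-up values with and without RLI: "21.41°±3.61° and 18.88 ° ± 4.32° in the two groups, respectively". The other inputs are significance level, power, allocation ratio and loss: "percentage of patients lost to follow-up were set at 0.05, 0.9, 1:1, and 20%, respectively". The result is a minimum: "at least 67 cases needed to be enrolled in the observation group and the control group, respectively".

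Part 1 groups follow from what is observed. Group A had no inversion at reduction, group B had inversion that persisted, and group C had inversion that resolved. They are then compared in pairs: "A combination consisting of any two of the groups was organized into cohorts". In part 3 (section 2.2.3.2) the cohort depends on whether intraoperative inversion exceeds a cut-off: "Patients undergoing open reduction procedures constituted the experimental cohort". Part 2 (section 2.2.2.2) is randomised in blocks.

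**The concern.** The pooled test estimates one common variance and uses it for both groups. This does no harm when the groups are of equal size. When sizes and variances both differ, the pooled standard error is wrong, in a direction set by which group is larger. If the larger group has the larger SD, the test is conservative and its confidence interval too wide. If the larger group has the smaller SD, the test rejects too often and its interval is too narrow.

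Both conditions are possible in part 1. The plan's own SDs differ, and they enter the sample size as two different values. The 1:1 ratio is an input to that calculation, but a retrospective classification by limbus status does not enforce it, and 67 is a floor without a ceiling. At stake is whether the 5% level and the 95% interval for the lead outcome are what they are labelled.

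**Working it through.** **Inputs from section 2.2.1.4.** RLI: mean 21.41, SD 3.61. No RLI: mean 18.88, SD 4.32. Significance level 0.05 (two-sided reproduces the stated figure), power 0.90, ratio 1:1, loss 20%.

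**The plan's own figure.** Difference: 21.41 − 18.88 = 2.53. Mean variance: (3.61² + 4.32²)/2 = (13.0321 + 18.6624)/2 = 15.847, so SD 3.981.

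n per group = 2 × (1.960 + 1.2816)² × 15.847 / 2.53² = 52.03, rounded up to 53. Then 53/0.80 = 66.25, rounded up to 67 per group, 134 in total. This matches the plan and uses both SDs.

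**Variance ratio.** 18.6624/13.0321 = 1.43.

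**Type I error of the pooled test.** Let n₁ be the RLI size (SD 3.61) and n₂ the no-RLI size (SD 4.32).

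- True variance of the difference: V_true = 13.0321/n₁ + 18.6624/n₂
- Pooled variance: s_p² = [(n₁ − 1) × 13.0321 + (n₂ − 1) × 18.6624]/(n₁ + n₂ − 2)
- Variance the pooled test uses: V_pool = s_p² × (1/n₁ + 1/n₂)
- r = √(V_pool/V_true); large-sample type I error = 2 × [1 − Φ(1.96 r)]

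Example, 201 RLI and 67 no-RLI:

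- s_p² = (200 × 13.0321 + 66 × 18.6624)/266 = 14.429
- V_pool = 14.429 × (1/201 + 1/67) = 0.2871
- V_true = 13.0321/201 + 18.6624/67 = 0.3434
- r = 0.9145, and 2 × [1 − Φ(1.792)] = 7.3%

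The simulated columns use normal data with equal means and 1,000,000 replicates per row. The ratios other than 1:1 are assumptions.

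| RLI / no-RLI | V_true | V_pool | r | Formula | Student's, simulated | Welch's, simulated |
|---|---|---|---|---|---|---|
| 67 / 67 (1:1) | 0.4731 | 0.4731 | 1.000 | 5.0% | 5.0% | 5.0% |
| 67 / 134 | 0.3338 | 0.3760 | 1.061 | 3.8% | 3.8% | 5.0% |
| 134 / 67 | 0.3758 | 0.3336 | 0.942 | 6.5% | 6.5% | 5.0% |
| 67 / 201 | 0.2874 | 0.3436 | 1.093 | 3.2% | 3.2% | 5.0% |
| 201 / 67 | 0.3434 | 0.2871 | 0.914 | 7.3% | 7.3% | 5.0% |

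The ratio drives the result, not the total. Splitting the planned 134 as 89 and 45 gives 6.5% or 3.8%; splitting it as 100 and 34 gives 7.2% or 3.2%. At a milder 67 versus 100, the figures are 4.2% or 5.9%.

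**Power at the planned 2.53°.** Student's: Φ(2.53/√V_true − 1.96 r). Welch's, to large-sample accuracy: Φ(2.53/√V_true − 1.96).

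- 67 / 201: 2.53/√0.2874 = 4.72. Student's Φ(4.72 − 2.14) = 99.5%; Welch's Φ(4.72 − 1.96) = 99.7%.
- 201 / 67: 2.53/√0.3434 = 4.32. Student's Φ(4.32 − 1.79) = 99.4%; Welch's Φ(4.32 − 1.96) = 99.1%. Student's small lead here comes from its inflated error rate.
- 67 / 67: both about 95.5% by simulation.

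**The case against.** A reader might infer that the main test runs at about 3% or 7% in parts 1 and 3. The documents do not support that, for four reasons.

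- **Ratio.** Those figures need an imbalance of about 3:1, which appears nowhere. The plan's only stated ratio is 1:1, where the level is 5.0%. A floor of 67 does not guarantee balance, but it does not imply 3:1 either.
- **Reach of the SDs.** They compare RLI with no RLI after closed reduction. They say nothing direct about group A against group C, or about open against closed reduction in part 3.
- **Strength of the SDs.** They are estimates from one earlier study whose group sizes are not given. If it had 30, 53 or 67 per group (assumed), a variance ratio of 1.43 would give a two-sided F-test p of about 0.34, 0.20 or 0.15. Unequal true variances are plausible, not shown.
- **Power.** A loss can be shown at a smaller difference: at 1.5° and 67 versus 201, 74% for Student's against 79% for Welch's. But 1.5° is not in the plan, and at 2.53° the loss disappears in practice.

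It can also be said that the article never uses the words pooled or equal-variance, that clinical papers use Student's name loosely, and that the full analysis plan may settle the variance option. This has some weight and is one reason why the point is minor. It does not remove the point, because the article does name a test and the name ordinarily denotes the pooled version. Nor is it a safeguard that the software may print both versions: the p-value that counts should be settled before the data are seen.

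What survives is the conditional statement for RLI against no RLI in part 1.

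**Conclusion.** The point holds as a minor improvement, not as an error that invalidates the analysis. The named test keeps its 5% level only if group sizes or variances turn out about equal. Part 1 fixes neither, and its own planning values point to unequal variances.

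The size is conditional on SDs of 3.61 and 4.32 being true, on approximate normality, and on assumed ratios. On those terms there is no distortion at 1:1 and a departure of roughly 1 to 2 percentage points in either direction at 2:1 to 3:1. For part 3 the mechanism is the same, but no magnitude can be given. For part 2, randomised in blocks, there is no evidence of a problem.

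**What to change.** In section 2.2.1.4, name Welch's unequal-variance t-test for the acetabular index. Make the same change in 2.2.3.4 as a precaution, since cohort sizes there also follow from limbus status, and in 2.2.2.6 only so that the three parts read alike.

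The cost is a change of test name in three sections. The sample size stays at 67 per group, because the two tests have the same power at equal sizes to within rounding. No data collection changes.
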